#### Clinical effects of intensified monitoring

- Decrease in CD4 count during failure in each arm
- Quality of life in each arm
- Any event of patient morbidity and mortality that can be related to immunological failure in each arm

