It is expected that intensified VL monitoring will detect therapy failure at an early stage, prior to selection of multiple resistance mutations. In those patients in which viremia is present, DLM is expected to identify patients with (nearly) undetectable plasma drug levels due to major non-adherence, in which the risk of drug resistance is expected to be lower. This will enable clinicians to provide intensified and tailored adherence counselling and prevent unnecessary resistance testing. Effective intensified adherence counselling has the potential to resuppress the VL to below 1000 copies/ml in over half of cases, if performed in an effective manner and in a setting of frequent VL monitoring.

When non-adherence is not detected by DLM, quick follow-up drug resistance testing will detect drug resistance prior to accumulation of resistance mutations and assure safe options for future treatment, preventing the use of more toxic regimens and therefore avoiding additional morbidity. It will also identify those patients in whom drug resistance mutations are absent, thus avoiding unnecessary treatment changes. Finally, as intensified monitoring is expected to reduce the duration of viremia during therapy failure it is expected to lower HIV transmission rates and transmission of drug-resistant HIV. Although the costs of intensified monitoring itself are higher, implementation of the strategy may be cost-effective or even cost saving by preventing unnecessary second-line therapy, reducing patient morbidity and mortality and reducing transmission rates.

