### 3.2 Secondary objectives

#### 3.2.1 Clinical effects of intensified monitoring

To assess the impact of the intensified monitoring strategy on (1) Quality of Life (QoL), (2) patient morbidity and mortality and (3) rates of immunological recovery. Clinical effects will be studied as a secondary objective as it is unknown if the follow-up duration will allow expected differences between arms to become apparent.

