#### 3.2.4 Cost-effectiveness of intensified monitoring

To assess the cost-effectiveness and incremental cost-effectiveness ratio (ICER) of the intensified monitoring strategy, taking into account the impact on QoL, morbidity and mortality, costs related to individual patient care such as diagnostic interventions, treatment switches and hospital admissions, and cost reductions on a population level as a result of averted new infections.

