## 4 STUDY DESIGN AND PATIENT POPULATION

### 4.1 Study format\*

The study format will be an open-label randomized controlled trial (RCT) in which HIV-1 infected patients initiating ART and already on ART will be enrolled. Enrolment will continue until 600 patients have been randomized. Patients initiating ART will be randomized after six months of ART and patients already on ART will be randomised at 6 months after the last viral load measurement. Patients in both arms will receive study visits every three months for a total follow-up duration of 18 months after randomisation to either of two study arms.

- Control arm: Standard of care HIV-1 treatment monitoring in accordance with South African NDOH guidelines. (see “5.1.2”)
- Intervention arm: Intensified treatment monitoring according to the treatment monitoring strategy under investigation. (see “5.1.3”)

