#### 5.2.7 Questionnaires

Questionnaires will be used to measure a variety of parameters relevant to the trial study objectives (see table 2). For data on adherence (e.g. number and reasons of missed doses, reasons and motives for non-adherence), drug toxicity and physical and mental wellbeing, a questionnaire developed by the AIDS Clinical Trial Group (ACTG) will be used. This validated self-report questionnaire has been included in several clinical trials and consists of a baseline and follow-up questionnaire. A modification of the ACTG baseline questionnaire will be used at enrolment, and a shortened version of the ACTG follow-up questionnaires will be used at month 3, 6, 9, 12, 15, 18, 21 and 24 (study end) in both study arms. Data on adherence from the standard pill count form that is applied at each drug pick-up visit (monthly or every 2 months) will also be collected.

Data relevant to the study objectives regarding social and psychological risk factors are partly covered by the ACTG questionnaires. A newly designed questionnaire will be used that will incorporate the sections from the ACTG questionnaires (mental and physical health), NIDS (socioeconomic status and family structure), CHAMP (substance abuse and sexual risk behavior). This questionnaire will contain item scales modified from the ACTG original, matched to local socio-economic and cultural context, as well as record several additional parameters such as stigmatization (Kalichman & Simbayi) and coping abilities (CISS). Data on Quality of life (QoL) of study participants will be used for evaluation of the cost-effectiveness of the trial intervention and will be recorded using the WHO QOL HIV (BREF) questionnaire and EQ5D questionnaire.

In a substudy participants who become lost to follow-up during the trial and who are successfully traced >28 days after a missed clinical visit (as per standard-of-care clinical procedures) are approached for informed consent to perform an additional questionnaire interview during a home visit.

Questions will be bundled in a comprehensive baseline and study end questionnaire (baseline and month 24), and a brief follow-up questionnaire which will be recorded per 3-monthly study visit (month 3, 6, 9, 12, 15, 18 and 21). In lost to follow-up patients who enter the substudy questionnaires will be recorded during a home visit. For a full overview of parameters and questionnaires, see table 2.

Table 2: overview of questionnaire data

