## 6 OUTCOMES AND ANALYSIS OF RESULTS

### 6.1 Virological and clinical effects of intensified monitoring

Virological outcomes will be differences between arms in (1) the number of drug resistance mutations present, (2) the selection of specific resistance mutations associated with multi-drug resistance (presence of the K65R mutation, or the presence of >1 NNRTI mutation) and (3) consequential loss of therapeutic options. Furthermore, (4) the rate of virological failure in the absence of drug resistance in both arms, unnecessary treatment switches averted in the intervention arm and unnecessary therapy switches made in the control arm will be assessed. An averted case of unnecessary switching will be defined as two sequential elevated VL results in the intervention arm without presence of resistance mutations. Assessment of unnecessary switching in the control arm can be ascertained by retrospective genotypic resistance testing.

Additional virological outcomes will be (5) the time on a failing regimen, defined as the time during which viremia > 1000 copies/mL is maintained after the first instance of a viral load >1000 copies/ml (6) The loss of second line therapeutic options over time in the presence of a failing regimen. Comparison of the extent of drug resistance between both groups will allow for assessment of the clinical consequences of resistance development in both arms. (7) The influence of genotypic resistance testing on the choice for a second line regimen. Genotypic resistance testing results enable the physician to make an informed decision with regard to a follow-up regimen to the first-line regimen. By comparing the chosen regimens in the intervention and control groups, the effect of the availability of genotypic resistance data on clinical decision-making will be compared. These outcomes can be compared between both arms as VL and CD4 measurements will be performed retrospectively in the control group, resulting in an equal frequency of measurements between both arms.

Clinical outcomes will be decrease in CD4 count during failure, QoL as measured using a validated QoL questionnaire, and recorded events of patient morbidity and mortality that can be related to immunological failure.

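### The morbidity and mortality outcome counts only events attributable to immunological failure, which is narrower than the objective it serves and rests on an unprotected causal judgement in an open-label trial

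*Protocol*

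**What the plan says.** The restriction appears twice. Section 6.1 of the protocol names, among the clinical outcomes, "recorded events of patient morbidity and mortality that can be related to immunological failure". The Summary's outcome list has "Any event of patient morbidity and mortality that can be related to immunological failure in each arm". The other clinical outcomes in both places are CD4 decline during failure and quality of life.

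The objectives and rationale are wider:

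- Section 3.2.1, giving the second and third clinical effects to be assessed, reads "2) patient morbidity and mortality and (3) rates of immunological recovery". No cause is specified for the morbidity or mortality.
- Section 3.2.4 describes the cost-effectiveness objective as "taking into account the impact on QoL, morbidity and mortality, costs related to individual patient care", again without a limit by cause.
- Section 2.2 expects the strategy to work partly by "preventing the use of more toxic regimens and therefore avoiding additional morbidity", and mentions "reducing patient morbidity and mortality and reducing transmission rates" among the reasons it may be cost-effective.

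Section 4.1 describes the trial as open-label. On data capture, Section 5.2.3 provides for WHO staging, symptom screening and the recording of other clinical events during follow-up. Section 5.2.7 says that for adherence data, "drug toxicity and physical and mental wellbeing, a questionnaire developed by the AIDS Clinical Trial Group (ACTG) will be used".

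**The concern.** An outcome should measure the objective it is attached to. Here the objective concerns illness and death of any cause, and the outcome keeps only a subset chosen by cause. Two consequences follow.

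First, whether an event counts depends on someone deciding that it can be related to immunological failure. In an open-label trial that decision can be made with knowledge of the arm. A difference between arms in how readily events are attributed would then look like a treatment effect, in either direction.

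Second, illness caused by a drug regimen is not immunological failure. The protocol names avoidance of more toxic regimens as a benefit, and exposure to second-line therapy is a planned contrast: Section 5.1.2 has control patients switch after two elevated viral loads without resistance testing, whereas Section 5.1.3 makes the intervention-arm switch depend on the resistance result. Toxicity events that follow from this contrast have no place in the listed event outcome.

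**Working it through.** The protocol states no event rate or power for morbidity or mortality, and Section 6.7.3 does not use this outcome, so there is no figure to reproduce. The check is mainly a comparison of texts.

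**Step 1: objective against outcome.**

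| Event type | Within objective 3.2.1? | Counted under 6.1 and the Summary? |
|---|---|---|
| Opportunistic illness linked to immune decline | Yes | Yes |
| Illness from regimen toxicity | Yes | No |
| Death from another cause | Yes | No |
| Death of uncertain cause | Yes | Depends on attribution |

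All-cause mortality is not a listed outcome in 6.1 or the Summary.

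**Step 2: safeguards on attribution.** The protocol does not define immunological failure for this outcome, state what makes an event relatable to it, or say who decides. It describes no independent review. A separate statistical plan could supply criteria, but it would not remove a restriction that the protocol itself sets.

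**Step 3: what uneven attribution could do (assumed inputs).** Let the true risk r of any event be equal in both arms, and let the share attributed be q_C (control) and q_I (intervention). The attributed risks are r·q_C and r·q_I, so the apparent risk ratio is q_I / q_C, whatever the value of r. With q_C = 0.80:

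- q_I = 0.80: 0.80/0.80 = 1.00
- q_I = 0.70: 0.70/0.80 = 0.875
- q_I = 0.60: 0.60/0.80 = 0.75
- q_I = 0.50: 0.50/0.80 = 0.625

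Swapping the arms inverts these ratios.

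The chance of a nominally significant result favouring the intervention (2.5% without bias) follows from the normal approximation with n = 300 per arm (Sections 5.1.2 and 5.1.3), ignoring loss to follow-up:

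Φ{ [ (p_C − p_I) − 1.96·√(2·p̄(1−p̄)/n) ] / √( [p_C(1−p_C) + p_I(1−p_I)]/n ) }

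For r = 0.10 and q_I = 0.60: p_C = 0.08, p_I = 0.06, p̄ = 0.07. The pooled standard error is 0.02083 and the unpooled 0.02082, so the argument is (0.02 − 0.0408)/0.0208 = −1.00 and the probability is about 16%. The same formula gives:

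| True risk r | q_I = 0.70 | q_I = 0.60 | q_I = 0.50 |
|---|---|---|---|
| 5% | 5% | 10% | 18% |
| 10% | 7% | 16% | 32% |
| 20% | 10% | 29% | 59% |

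**Step 4: the same point with few events (assumed counts).** Suppose 12 events per arm, one third attributed: 4 v 4, ratio 1.0. Reclassifying two events in one arm gives 6/4 = 1.5 or 2/4 = 0.5. With 300 per arm, the standard error of the log ratio is √(1/6 + 1/4 − 2/300) = 0.64 for 6 v 4 and √(1/2 + 1/4 − 2/300) = 0.86 for 2 v 4. The 95% intervals are about 0.43 to 5.3 and 0.09 to 2.7. The all-cause ratio stays at 12/12 = 1.0 however causes are assigned.

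**The case against.** The case on the other side has several sound parts.

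- **The importance is limited.** This is one component of a secondary objective. Section 3.2.1 says it is unknown whether follow-up will be long enough for clinical differences to appear. This stands.
- **The size is assumed.** No event rates are given, and with few events the intervals in Step 4 are too wide to mislead much. The larger false-positive figures need both high event risks and wide gaps in attribution. This stands; the figures show the mechanism, not an expected bias.
- **Attribution rules may be written elsewhere.** That is possible, but the restriction to a cause-specific subset is fixed in this protocol.

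Three stronger readings are tempting, and the documents do not support them.

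- A reader might infer that the extra viral load, drug-level and genotype results in the intervention arm will drive attribution. Those tests concern virological failure, adherence and resistance. Immunological failure would ordinarily be read from CD4, which Table 4 schedules at months 6, 12 and 24 without distinction by arm, and Section 6.1 intends equal measurement frequency. Visits and clinical assessments are also the same in both arms. Knowledge of the arm remains a risk; that particular asymmetry is not shown.
- A reader might infer that the cost-effectiveness ratio is directly biased. Section 6.3 extends the Markov model with known South African evidence on quality of life and mortality, and nothing says the attributed event count is the input.
- A reader might infer that toxicity effects cannot be shown at all. Quality of life is a listed outcome without limit by cause and is measured every three months (Table 2), the questionnaire asks about toxicity, and unnecessary switching is itself a virological outcome. What is missing is an event outcome for toxicity.

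**Conclusion.** The point holds as a mismatch between outcome and objective. As written, 6.1 and the Summary measure a cause-specific subset of the morbidity and mortality that 3.2.1 sets out to assess. They make that subset depend on an attribution with no described protection in an open-label trial, and they leave no event outcome for toxicity-related morbidity that the rationale expects to fall.

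That attribution would involve judgement by someone aware of the arm is an inference, since no assessor is named; it follows from the outcome wording and the open-label design. The size cannot be derived from the protocol. Under the assumed attribution shares, the apparent risk ratio with no true effect ranges from 1.00 to 0.625, or the inverse. The virological outcomes and the sample size are untouched. This is a cheap improvement to a secondary outcome and does not threaten the trial's main conclusions.

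**What to change.** In Section 6.1 and the Summary, define the clinical event outcome as all-cause mortality and all recorded morbidity by arm: new WHO stage events, other recorded clinical events, and questionnaire-reported toxicity. Keep events related to immunological failure as a secondary breakdown of that total. A masked adjudication step is not needed, because the main comparison no longer depends on attribution.

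The data are largely provided for: staging and other events in 5.2.3, toxicity in 5.2.7, a definite study outcome after tracing in 5.3.1.8, and permission to collect morbidity and mortality data after withdrawal in 5.5. Table 3 marks clinical outcomes at baseline only, so that row should be checked against 5.2.3 and 5.3.1.3, which have clinical data recorded at follow-up visits.

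The cost is a change of outcome wording, plus some noise from events unrelated to monitoring. All-cause mortality removes the dependence on attribution, but it still needs deaths to be ascertained equally well in both arms.

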### 6.2 Feasibility of intensified monitoring

With the results of this study, it will be possible to assess the feasibility of intensified monitoring in LMIC and identify practical and logistical barriers to implementation of the approach in low- and middle-income countries. Several outcomes will be studied: (1) The practical and logistical implementation challenges as reported by involved research health care

workers. (2) The time needed to set-up and perform a basic local validation of the on-site drug level assay (3) The realization of expected turnaround times, specifically the turnaround time of on-site testing (drug-level measurement) and centralized testing (more frequent viral load measurements and drug resistance testing on DBS). (4) The effect of genotyping and drug level assessment results on the choice of second line therapy, in which it will be determined if the increased availability of information regarding treatment is interpretable and useable in LMIC clinical practice by interviews of the involved medical personnel (physicians and clinical nurses). In addition the time to report of results and actual clinical intervention will be evaluated. The overall results of this evaluation will be to inform policy makers both in South Africa and abroad. Scientific peers and laboratory staff will be instructed on pitfalls and successful approaches.

### 6.3 Cost-effectiveness of intensified monitoring

The cost increases associated with the intensified monitoring strategy will be compared with the (estimated) cost reductions by prevention of unnecessary switches to a more costly regimen and differences in other study outcomes between arms. To evaluate the cost-effectiveness of the intensified monitoring strategy we will assess the effects of the intensified monitoring strategy on reduction of resistance accumulation and unnecessary treatment switches in a model-based approach with several levels of detail. The first assessment will concern the net cost of implementing tailored patient management based on DBS for resistance genotyping. A Markov model will be developed to estimate the costs over a fixed time period following initiation of ART. Secondly, we will assess the cost-effectiveness of implementing decentralized drug level testing. Here, we will extend the Markov model with known evidence on health outcomes in South Africa, i.e. quality of life using a standardized item scale and mortality. With the extended model the costs and effects, in terms of life-years and quality-adjusted life-years (QALYs) gained, as well as the incremental costs and ICER of (different components of) the intensified monitoring strategy will be estimated. Finally, we will analyze cost-effectiveness from the societal perspective and take indirect costs and benefits into account, e.g. costs and benefits that are generated by the impact of treatment on patients' productivity and participation in society. To fully take indirect effects into account dynamic transmission modeling is necessary. Sensitivity analyses will be performed in order to ascertain how the (cost)-effectiveness of various monitoring schemes depends on behavioral parameters, on treatment uptake and adherence, and other key model parameters.

#### 6.4 Effect on transmission of HIV

Using a transmission dynamic model we will assess the effects of monitoring strategies and reduction in resistance development at the population level by studying the relationships between the monitoring strategies, infectivity of patients on treatment and HIV incidence and prevalence. We will design a model that is structured by age and sex, and that explicitly takes CD4+ counts and viral load into account. The model will be calibrated to HIV prevalence in the study region using data available through reports from the South African NDoH. We will estimate parameters pertaining to diagnosis rates, uptake of treatment, adherence to treatment and monitoring from the data collected during this study. We will then analyse various monitoring and treatment scenarios to analyse the impact of different monitoring schemes on HIV incidence and prevalence in the future. Model output on incidence stratified by age and sex can then be used as input for the Markov model for cost-effectiveness assessment. We will also study the possible spread of resistant strains in a population with a high prevalence of treatment sensitive strains. We will assess how spread of resistant strains may depend on treatment uptake and adherence parameters, and how transmission of resistant strains impacts on the (cost)-effectiveness of specific monitoring schemes. Particular focus will be on how to design a monitoring scheme that minimizes the risk of spread of resistant strains in the population while still being feasible and cost-effective. We will study which parameters are key for such a scheme and how it depends on disease specific characteristics such as the infectivity during early HIV infection and heterogeneity in the population with respect to sexual risk behavior and testing behavior. Short and long-term impact on HIV incidence will then be associated with impact on disease burden in the population and with cost-effectiveness of those monitoring strategies.

#### 6.5 Risk factors for therapy failure

By multivariate (regression) analysis of biological parameters such as viral suppression, drug levels and drug resistance social, economical and psychological risk factors, indicators of suboptimal adherence and therapy failure will be ascertained. Data on stigmatization and coping strategies will be used to assess non-adherence risks. These data in their turn will be analysed in order to determine whether adherence is a mediating or moderating factor in defining the patient health outcomes (mental and physical health and QoL). In addition, multivariate analysis of the relationship between risk factors, adherence, patient health and QoL will provide the opportunity for local validation of these item scales and for development of a scoring model for the risk of therapy failure.

## 6.6 Determinants of therapy failure

In depth studies of virological, immunological and pharmacological markers on stored PBMCs and plasma are planned to gain insight in virological, immunological and pharmacological determinants underlying therapy failure. Detailed outcomes that will be measured as part of these sub studies will be described in an amendment to the current protocol.

